**Table 2: Power Estimates.**

| p1* | p2* | Difference | Power, n=24 | Power n=20 |
|------------|------------|-------------------|--------------------|-------------------|
| .25        | .5         | .25               | .325               | .261              |
| .35        | .6         | .25               | .307               | .247              |
| .45        | .7         | .25               | .313               | .252              |
| .2         | .5         | .3                | .479               | .391              |
| .3         | .6         | .3                | .445               | .362              |
| .25        | .6         | .35               | .595               | .497              |
| .35        | .7         | .35               | .585               | .488              |
| .2         | .6         | .4                | .740               | .640              |
| .3         | .7         | .4                | .719               | .619              |

\*p1 and p2 are the proportion of subjects in comparison 1 vs. comparison 2.

### Data Analysis:

All study data will be transcribed from paper surveys and entered into a REDCap database for data management. We will perform random screening of entered data to ensure accuracy. At the time that the REDCap database is translated into a SAS database for data analysis, the 2 main intervention codes (i.e., Acidil vs. placebo and standard vs. expanded interview) will be recoded by a member of the study team who did not have any subject contact ([name]) so that the principle data analyzer ([name]) is blinded to all study group assignments during the data analysis process. Initial analysis will include descriptive statistics assessing the baseline demographics, GERD and dyspepsia symptom frequency and severity, and HRQL among subjects in each of the 4 groups. All analyses described below will be intent-to-treat analyses and include an interaction term to account for possible interaction of the 2 main interventions in this study. The SAS database will not include any PHI and will be stored on the study investigator's H drive and thus will be password protected and behind a secure firewall.

**Hypothesis 1:** This study design will be both safe and feasible and subject recruitment will not be difficult.

Study safety will be established if there are no major adverse events attributed to Acidil and no statistically significant increase in minor adverse events between the Acidil and placebo groups. Feasibility will be established if we can demonstrate recruitment and retention of >90% of subjects within the pre-specified 6-12 month time frame.

**Hypothesis 2a:** Compared to subjects receiving placebo, more subjects receiving Acidil will experience a 50% or greater improvement in GERD symptom severity during the last 7 days of the study compared to baseline.

A common measure for assessing treatment efficacy in GERD trials is assessment of the percent of subjects with a 50% or greater improvement in heartburn symptom severity (based on summation of symptom scores over time) using daily symptom diaries. We will perform this assessment by combining responses to the daytime heartburn, nighttime heartburn, and acid regurgitation questions on the daily symptom diaries for the last 7 days of the study compared to baseline. We will compare groups 1 and 3 with groups 2 and 4 using a logistic regression analysis and including an interaction term for the two study interventions. If there is no difference between groups, we will perform a secondary analysis using the GERD symptom severity score as a continuous variable to evaluate for potential trends.

**Hypothesis 2b:** The dynamic trajectory of symptom changes over time will differ between the Acidil and placebo groups. These differences may manifest as oscillations in symptoms in the Acidil group during the 2 week trial period, as well as changes in non-GERD and non-dyspeptic symptoms.

To assess for dynamic changes in treatment effects over time that may not be visible in end-point analyses such the one described in 2a above, we will perform a repeated measures analysis using generalized estimating equations and incorporating a time by treatment interaction term that will allow us to examine changes in GERD and dyspepsia symptom severity for the Acidil (groups 1+3) vs. placebo (group 2+4) group over the entire 2 week study period as well as look for differences in the number and frequency of non-GERD and non-dyspeptic symptoms based on data in the daily symptom diaries.

We will also assess the mean number of days without heartburn symptoms during the trial period for groups 1+3 and 2+4 as well as the mean number of days without dyspeptic symptoms during the

trial period (again groups 1+3 and 2+4) using the data from the GERD symptom diary.

**Hypothesis 2c:** Subjects receiving Acidil will report greater improvement in disease-specific and overall quality of life compared to the placebo group.

We will compare GERD-HRQL, Nepean Dyspepsia Index, and SF-12 scores between the Acidil and placebo groups (1+3 and 2+4), incorporating an interaction term for the two main treatment effects, using ANOVA.

**Hypothesis 3a:** Compared to subjects receiving the standard clinical interview, more subjects receiving an expanded clinical interview will have a 50% or greater improvement in GERD symptom severity during the last 7 days of the study compared to baseline.

We will perform an analysis analogous to that for hypothesis 2a above by combining responses to the daytime heartburn, nighttime heartburn, and acid regurgitation questions for the last 7 days of the study compared to baseline on the daily symptom dairies comparing groups 1 + 2 with groups 3 + 4 using a logistic regression analysis and including an interaction term for the two study interventions.

**Hypothesis 3b:** Subjects receiving an expanded clinical interview will report greater improvement in disease-specific and overall quality of life compared to subjects receiving a standard clinical interview.

We will compare GERD-HRQL, Nepean Dyspepsia Index, and SF-12 scores between the standard (groups 1 + 2) and expanded (groups 3 + 4) interview groups, incorporating an interaction term for the two main treatment effects, using ANOVA.

**Hypothesis 3c:** Subject beliefs and expectations pre-treatment will partially explain changes in GERD and dyspeptic symptoms in the expanded vs. standard interview groups but not in the Acidil vs. placebo groups.

We will perform a logistic regression analysis including subjects' pre-treatment belief in CAM and scores on the credibility questionnaire using greater than 50% improvement in heartburn symptom frequency or severity during the last 7 days of the study compared to baseline (based on the daily symptom dairies) as the outcome. Due to the small sample size, we will be unable to adjust for potential confounders.

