### B1. PURPOSE OF PROTOCOL

The purpose of this study is to investigate the effects of a) a homeopathic supplement marketed for heartburn symptoms (Acidil) and b) components of the placebo response (the doctor-patient interaction and belief/expectation) on symptoms and health-related quality of life (HRQL) in patients with gastroesophageal reflux disease (GERD). This study is designed as a pilot trial to assess safety and feasibility and to provide preliminary estimates of effect sizes in anticipation of conducting a larger trial in the future.

**Aim 1:** To determine the safety and feasibility of conducting this 2x2 factorial design randomized controlled trial in this patient population.

**Hypothesis 1:** This study design will be both safe and feasible and subject recruitment will not be difficult (i.e., no significant adverse events and greater than 90% of those who enroll will complete the study protocol).

**Aim 2:** To determine whether changes in GERD-specific, dyspeptic, and overall symptoms and HRQL are significantly different between subjects receiving Acidil and subjects receiving an identical placebo.

**Hypothesis 2a:** Compared to subjects receiving placebo, more subjects receiving Acidil will experience a 50% or greater improvement in GERD symptom severity during the last 7 days of the study compared to baseline.

**Hypothesis 2b:** The dynamic trajectory of symptom changes over time will differ between the Acidil and placebo groups as expected according to homeopathic theory.

**Hypothesis 2c:** Subjects receiving Acidil will report greater improvement in disease-specific and overall quality of life compared to the placebo group.

**Aim 3:** To determine whether changes in GERD-specific, dyspeptic, and overall symptoms and HRQL are significantly different between subjects receiving an expanded clinical interview similar to a homeopathic consultation (enhanced physician-patient interaction) vs. a standard allopathic interview, and to determine whether any treatment responses are mediated by preconceived beliefs and expectations regarding treatment efficacy.

**Hypothesis 3a:** Compared to subjects receiving the standard clinical interview, more subjects receiving an expanded clinical interview will have a 50% or greater improvement in GERD symptom severity during the last 7 days of the study compared to baseline.

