Homeopathic medicines are generally regarded as very safe, due to the low concentrations of active ingredients present, with adverse event rates generally estimated to be 3% or less and serious adverse events extremely rare (11, 14). In the United States, homeopathic medicines are regulated by the FDA under the 1938 Food, Drugs, and Cosmetics Act (15). The majority of homeopathic medicines are available OTC without a prescription required. According to the manufacturer (Boiron) of the product to be used in this study (Acidil), there have been no adverse event reports for this supplement over the last 10 years in the United States.

Despite the relative safety of homeopathic medicines, certain types of treatment reactions are commonly recognized by the homeopathic community. These include aggravations and provings. An aggravation is a transient aggravation of a patient's symptoms followed by a marked improvement in symptoms and is felt to be a positive prognostic sign of healing. A proving occurs when a patient manifests symptoms that the homeopathic medicine is designed to treat and usually occurs when a patient has received too much of the medicine and/or the medicine is poorly matched to the patient's symptoms. Aggravations and provings may explain the dynamic oscillations seen in patients' symptoms in the homeopathy arms, but not the placebo arms, of some randomized controlled trials (16, 17). These observations complicate the interpretation of treatment outcomes and may account for some inconsistent results in prior homeopathic studies. Thus, in our study, we propose to monitor dynamic changes in symptoms over time as well as conduct endpoint analyses.

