#### First Study Visit (Time 1):

When a potential subject arrives at the study site, the diary will be reviewed to ensure that it meets eligibility criteria (symptoms at least 3 days out of 7 and symptom frequency and severity recorded on at least 6 days of 7) and the individual will undergo a final in person eligibility assessment reviewing the criteria discussed during the phone screen. Subjects deemed ineligible will be thanked for their effort, informed that they are not eligible, receive parking validation and be dismissed.

Eligible subjects will be formally consented, have blood drawn (if they opt to participate in the repository study described in a separate application), and complete a series of baseline questionnaires (demographics, medication and supplement use, GSRS, Nepean Dyspepsia Index, GERD-HRQL, SF-12, MYMOP, credibility questionnaire, CAMBI, see Table 1 below). Next, subjects will be randomized to one of the 4 treatment groups and receive either the standard or expanded interview in a single-blinded fashion (the study physician will be aware of assigned interview type, but the subject will not). The clinical interview will be audio and video recorded (pending subject permission) to permit subsequent assessment of fidelity to the treatment protocol.

After the interview, subjects will complete additional questionnaires (CARE, credibility questionnaire, see Table 1). Finally, subjects will receive the study medication (Acidil or placebo) in a double-blinded fashion (neither the study physician nor the subject will be aware of treatment assignment) and rescue antacid. The study physician, or another member of our research team, will provide medication education. All subjects will receive the same instructions for how to take the study medication and rescue antacid, will be provided with a new study diary, and their 2 week follow-up appointment will be confirmed. Study subjects will be contacted 7 days following the first study visit to confirm that they are taking the study medication, completing their daily diary, and not experiencing any marked adverse effects. The first study visit is anticipated to last 1-2.5 hours.

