#### Testing and Outcome Measures:

All testing will be conducted at the BIDMC GCRC on east campus. A schedule of testing is outlined in the table below. All testing will be conducted by study staff and physicians who are blinded to treatment assignment (except for the study physician who will know whether the patient is receiving the standard or expanded interview).

| Study Measures and Timepoints                                                                                                                                                                                                           |                                                                       |                                                                                        |            |    |    |   |
|------------------------------------------------------------------------------------------------------------------------------------------------------------------------------------------------------------------------------------------------|-----------------------------------------------------------------------|----------------------------------------------------------------------------------------|------------|----|----|---|
| #                                                                                                                                                                                                                                              | Measure/Procedure                                                     | Description/Rationale                                                                  | 0          | 1a | 1b | 2 |
| 1                                                                                                                                                                                                                                              | Study Diary                                                           | Daily dairy assessing GERD, dyspeptic, & other symptoms and medication use             | Throughout |    |    |   |

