#### Monitoring of Adverse Events and Patient Safety:

Any and all adverse events will be reported to our independent safety and monitoring board. No interim analyses of study efficacy are planned due to the pilot nature of this study.

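### Hypothesis 1 carries two different safety criteria, and the one in the analysis section counts only major events attributed to Acidil, then calls safety established on 12 subjects

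*Protocol*

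**What the plan says.** Aim 1 in section B1 is "To determine the safety and feasibility of conducting this 2x2 factorial design randomized controlled trial in this patient population". Hypothesis 1 beneath it explains safe and feasible as "no significant adverse events and greater than 90% of those who enroll will complete the study protocol". That wording has no condition on arm or on cause.

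In section B3.B, under Data Analysis, Hypothesis 1 is restated without that explanation and a rule follows: "Study safety will be established if there are no major adverse events attributed to Acidil", and in addition "no statistically significant increase in minor adverse events between the Acidil and placebo groups". So the major-event half depends on a causal attribution, and the minor-event half on a comparison between randomised arms.

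On who might attribute an event, the protocol gives only fragments. On the tablets, "neither the study physician nor the subject will be aware of treatment assignment". On reporting, "Any and all adverse events will be reported to our independent safety and monitoring board". Section B5 adds reporting to the IRB and a safety review by a two-person independent committee about half way through recruitment. None of these places says who decides that an event is attributed to Acidil.

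The Overview and the Sample Size Justification plan 6 subjects in each of 4 groups, 24 in all.

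**The concern.** Safety is half of the first aim, and the protocol gives it a pass/fail rule. With two rules for the same hypothesis, the same data can yield two verdicts, and an analysis plan cannot follow both. The rule in the analysis section is also narrower than the aim. Aim 1 concerns the safety of conducting the trial, which includes the placebo arm and the rescue antacid that every subject receives, but the rule looks only at events ascribed to one product. Randomisation supplies a count by arm that needs no causal judgement. The rule uses such a comparison for minor events and not for major ones. Finally, a zero count in a very small arm is to be reported as safety established, which readers planning the larger trial could take as more than it is.

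**Working it through.** **Step 1. The two criteria on the same data.** The protocol gives no numerical figure for this rule, so there is none to reproduce. Assume that *significant* in B1 covers *major* in B3.B.

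| Single major event on study | B1, Hypothesis 1 | B3.B, major-event half |
|---|---|---|
| Acidil subject, attributed to Acidil | fails | fails |
| Acidil subject, judged unrelated | fails | satisfied |
| Placebo subject, not attributed to Acidil | fails | satisfied |

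The criteria disagree in two of the three cases.

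**Step 2. How often they could disagree.** The protocol gives no major-event rate. Its only rate is 3% or less for any adverse event of homeopathic medicines (section B2, Homeopathy). As an assumption, take a per-subject major-event rate p of 1% to 5%, equal in both arms, with a share s of Acidil-arm events attributed to Acidil and subjects independent.

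- Chance that B1 fails on major events: 1 − (1 − p)^24.
- Chance that the B3.B major-event half fails: 1 − (1 − ps)^12.

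An attributed event is also an event, so the difference is the chance that the two criteria disagree.

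| p | B1 fails | B3.B fails, s = 1 | Disagree | B3.B fails, s = 0.5 | Disagree |
|---|---|---|---|---|---|
| 1% | 21.4% | 11.4% | 10% | 5.8% | 16% |
| 3% | 51.9% | 30.6% | 21% | 16.6% | 35% |
| 5% | 70.8% | 46.0% | 25% | 26.2% | 45% |

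With s = 1 the whole disagreement comes from the placebo arm. These figures measure how far apart the two wordings are. They do not measure wrong attribution, because s below 1 may simply mean that some events truly are unrelated.

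**Step 3. What zero events can show.** Acidil subjects are groups 1 and 3: 6 + 6 = 12. With zero events in n subjects, the exact upper bound solves (1 − p)^n = α.

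- One-sided 95%, n = 12: 1 − 0.05^(1/12) = 0.221.
- Upper limit of a two-sided 95% interval, n = 12: 1 − 0.025^(1/12) = 0.265 (0.2646 before rounding, so 26%).
- One-sided 95%, all n = 24 subjects: 1 − 0.05^(1/24) = 0.117.

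The best result possible on Acidil is therefore compatible with a true major-event rate of up to about one in five. This holds whoever attributes events and however well.

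**The case against.** The strongest reply is that there is no real conflict. B1 gives a parenthetical gloss in a list of aims, the analysis section gives the operative rule, and *significant* may be shorthand for the fuller rule. This stands in part: the contradiction depends on *significant* including major events whatever their cause. But the gloss is introduced as the meaning of the hypothesis, it sits under an aim about the whole trial, and nothing in the text limits it to attributed events. Nor should B1 be read as requiring no adverse events at all; it is limited to significant ones.

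A reader might infer that blinded staff make the attribution. The documents do not say so. The statement that "All testing will be conducted by study staff and physicians who are blinded to treatment assignment" concerns testing, and the independent board or committee could attribute events, with its own blinding unstated. Blinded causality assessment would not be a flaw in any case, and naming the assessor is often left to an analysis or monitoring plan.

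A reader might also infer that the background biases the judgement, because it describes a transient aggravation as "felt to be a positive prognostic sign of healing". That passage reports a view held among homeopathic practitioners about passing symptom worsening. Nothing suggests that major events would be excused on that ground.

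It is also fair to say that all adverse events are reported, that the committee can end the trial, that nothing prevents a table of major events by arm, and that a small zero count is a limit of any pilot. These points lower the risk to subjects. They do not settle which criterion decides Hypothesis 1, or justify calling safety established.

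**Conclusion.** The point holds as a contradiction between two stated criteria, with an overstated conclusion attached to one of them. If *significant* includes *major*, a placebo-arm major event or an unrelated one on Acidil gives opposite answers under B1 and the major-event half of B3.B. The size of the second problem needs no assumed event rate: 0 of 12 excludes only rates above 22% one-sided, or 26% two-sided. The disagreement chances of 10% to 45% rest on assumed rates of 1% to 5%, equal arms and the stated attribution shares, and serve only as illustration.

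The documents do not support the stronger reading that the attribution filter would hide harm caused by Acidil. They give no major-event rate and no attribution process, and an event left unattributed may have been left so correctly. This should be corrected, but it is a matter of the decision rule and its wording, not evidence that safety reporting is deficient.

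**What to change.** 1. Use one criterion, with the same severity term, in Hypothesis 1 of section B1 and in Hypothesis 1 under Data Analysis.
2. Under Data Analysis, report all major adverse events in every randomised subject, by arm and regardless of attribution. Show attribution to Acidil as a descriptive column beside the counts.
3. For this component, replace the statement that safety will be established with the observed count per arm and its exact upper 95% bound. For example, 0 of 12 would be reported with a one-sided upper bound of 22%.

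The cost is protocol wording and one simple exact calculation; the events are already to be reported to the board and the IRB. The small downside is that unrelated major events will appear in the count and must be explained in the text rather than left out.

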### B3. DESCRIPTION OF RESEARCH PROTOCOL

#### A. Study Design – Overview, Methods, Procedures

##### Overview

We propose to conduct a single-center, pilot feasibility, 2x2 factorial design randomized controlled trial assessing the effect of a homeopathic supplement (Acidil) and components of the placebo response (doctor-patient interaction and beliefs/expectations) on symptoms and HRQL in patients with GERD over a 2 week time interval. The Acidil vs. placebo intervention will be double-blinded and the standard vs. expanded interview intervention (doctor-patient interaction) will be single-blinded. Randomization will be by permuted block randomization with block sizes of 4 and 8. We plan to enroll 6 patients into each group for a total of 24 subjects in the study according to the adjacent scheme. Subjects will be evaluated in the GCRC at BIDMC at two timepoints: baseline and at 2 week follow-up.

|                    | Acidil  | Placebo |
|--------------------|---------|---------|
| Standard Interview | Group 1 | Group 2 |
| Expanded Interview | Group 3 | Group 4 |

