## **B. Statistical Considerations**

### **Sample Size Justification:**

We will screen a sufficient number of subjects to consent/enroll 24 subjects total into the study, 6 subjects in each of the 4 groups. This number was determined to ensure that we can complete enrollment within a 6-12 month time frame to assess study feasibility as our primary outcome.

As this is a pilot feasibility study, we do not anticipate having adequate power to show significant differences in treatment effects between groups, but do hope to generate estimates of effect sizes and demonstrate trends. Our chief secondary outcome will be the percent of subjects with 50% or greater improvement in heartburn symptom severity for the last 7 days of the study compared to baseline (compare groups 1+3 vs. groups 2+4 [Aim 2a] and groups 1+2 vs. groups 3+4 [Aim 3a]). We will also assess the percent of subjects with dynamic changes in heartburn symptom severity during the study period compared to baseline (compare groups 1+3 vs. groups 2+4 [Aim 2b]).

Table 2 illustrates power estimates using the Fisher exact test for between group differences ranging from 0.25 – 0.4 for an alpha of 0.05 and sample sizes of 24 subjects and 20 subjects per group (combining groups 1+3 and 2+4 or groups 1+2 and 3+4 for all analyses). We anticipate that we will have 30-50% power to detect a difference between groups. These power calculations are based on the assumption of no interaction effect.

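### Safety is to be declared established partly on a non-significant comparison of minor adverse events in 12 versus 12 subjects, which cannot support that conclusion

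*Protocol*

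**What the plan says.** The operational rule is in section B3.B, Data Analysis, under Hypothesis 1. It has two parts joined by *and*. The first is "Study safety will be established if there are no major adverse events attributed to Acidil"; the second is "no statistically significant increase in minor adverse events between the Acidil and placebo groups". The rule names no test, significance level, sidedness or margin, and does not say whether minor events are counted as events or as subjects affected.

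Section B1 puts the same hypothesis differently, as "no significant adverse events and greater than 90% of those who enroll will complete the study protocol". That wording mentions neither attribution to Acidil nor a between-arm comparison.

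On size, the Overview in B3.A says "We plan to enroll 6 patients into each group for a total of 24 subjects in the study", and the Sample Size Justification repeats it as "consent/enroll 24 subjects total into the study, 6 subjects in each of the 4 groups". That section concedes inadequate power for treatment effects. It does not extend the caveat to the safety rule.

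**The concern.** A non-significant result means the data did not exclude equality. It does not mean they excluded harm. A rule that concludes safety from non-significance becomes easier to satisfy as the trial gets smaller, which is the wrong direction for a safety criterion.

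Safety is half of Aim 1, and the pilot is meant to inform a larger trial. The protocol also foresees transient worsening of symptoms and provings on the active product (B2, Homeopathy; B5), so an excess of minor events on Acidil is a realistic possibility. At stake is a prespecified statement that safety has been established, carried into the next trial on data that could not have shown otherwise unless the excess was very large.

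**Working it through.** **Inputs from the protocol.** There are 6 subjects per cell. Acidil is groups 1+3 and placebo is groups 2+4, so 6 + 6 = 12 per arm. The only adverse event rate given is 3% or less for homeopathic medicines in general (B2, Homeopathy).

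**Assumptions.** The placebo minor-event rate is taken as 10%, with 3% as an alternative. The Acidil rates of 30% to 50% are illustrative. The analysis counts subjects with at least one minor event and uses Fisher's exact test at 0.05, both two-sided and one-sided.

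**The plan's nearest figure.** No power is stated for adverse events. The efficacy power table uses Fisher's test "for an alpha of 0.05" with "sample sizes of 24 subjects and 20 subjects per group". The arcsine approximation is Φ(√(2n)·[asin√(p2 − 1/(2n)) − asin√(p1 + 1/(2n))] − 1.96). For 0.2 versus 0.5 with n = 24 it gives Φ(6.928 × (0.7646 − 0.4892) − 1.96) = Φ(−0.052) = 0.479, as printed in Table 2. So the plan's own convention is two-sided 0.05. The same formula with the 12 per arm actually enrolled gives Φ(4.899 × (0.7437 − 0.5139) − 1.96) = Φ(−0.834) = 0.202.

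**Probability that the minor-event condition is met.** For placebo rate p and Acidil rate q, sum Bin(a; 12, p) × Bin(b; 12, q) over all pairs (a events on placebo, b on Acidil) that do not give a significant excess on Acidil. Exact enumeration gives:

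| True rates, placebo → Acidil | Two-sided | One-sided |
|---|---|---|
| 10% → 30% | 0.905 | 0.803 |
| 10% → 40% | 0.767 | 0.614 |
| 10% → 50% | 0.575 | 0.400 |
| 10% → 60% | 0.361 | 0.209 |
| 3% → 30% | 0.798 | 0.616 |

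These figures are for the second condition alone. The joint rule also needs the first condition, so its probability of being met cannot exceed them.

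**What this means in counts.** With no event on placebo, the one-sided p-value for 4 of 12 on Acidil is C(12,4)/C(24,4) = 495/10,626 = 0.047, and the two-sided value is twice that, 0.093. For 5 of 12 it is 792/42,504 = 0.019 one-sided and 0.037 two-sided. So 4 versus 0 satisfies the condition two-sided and fails it one-sided. The same holds for 6 versus 1 (0.069 two-sided, 0.034 one-sided). The unstated sidedness would therefore decide the safety verdict in such cases.

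**Direction with sample size.** For 10% → 40%, two-sided, the condition is met with probability 0.398 at 24 per arm, 0.767 at 12 and 0.977 at 6.

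**The major-event condition.** With no event in 12 subjects, the exact upper limit solves (1 − π)^12 = α. One-sided 95%: 1 − 0.05^(1/12) = 0.221. Two-sided 95%: 1 − 0.025^(1/12) = 0.265.

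**The case against.** The best defence is that this is a pilot, that it admits its low power, and that participants are not protected by this test. Adverse events go to an independent board and to the IRB, a committee reviews safety about half way through recruitment and can stop the study, diaries record side effects, and subjects are contacted at day 7. All of that is in the protocol, and a reader should not infer that participants are left unmonitored. But it concerns conduct. The power caveat is confined to treatment effects, and neither it nor the oversight changes what the final rule concludes.

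Three stronger readings are tempting and are not supported.

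- **The rule is passed almost whatever the truth is.** It is not. From 10% to 60% the minor-event condition is met only 36% of the time two-sided and 21% one-sided. Because the criterion is worded as an increase, a one-sided test is a fair reading, and under it a rise from 10% to 50% is caught 60% of the time. A major event attributed to Acidil would also fail the rule.
- **Safety is the primary outcome.** The Sample Size Justification gives that place to feasibility. Safety shares Aim 1 with it.
- **B1 and Data Analysis prescribe two competing analyses.** B1 is a brief parenthetical statement of the hypothesis and Data Analysis is the working rule. They can give different answers, for instance after a major event judged unrelated to Acidil, but aligning the wording settles that.

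The upper limit of 22% or 26% applies to any arm of 12 with no events and is not itself an error. It matters only because the protocol would call that result established safety. A separate analysis plan, not available here, may well add intervals, but the decision rule is fixed in the protocol.

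**Conclusion.** The point holds, and it should be fixed. As written, the plan can conclude that safety is established from data that cannot support it. At 12 per arm, increases of about 30 percentage points or less in the minor-event rate would more often than not go unflagged under either sidedness. For a rise of 40 points from 10%, that is true of the two-sided test (58% unflagged) but not of the one-sided test (40%). The percentages depend on the assumed Fisher test, on the assumed rates and on counting subjects, and they bound the joint rule from above. The flaw in the reasoning does not depend on them. Its effect is limited to the strength of the safety claim; no efficacy estimate rests on this rule.

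**What to change.** In Data Analysis, Hypothesis 1, remove the significance-test criterion and the statement that safety will be established. In its place:

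- Report the number of subjects with minor and with major adverse events in each arm, with exact 95% confidence intervals, and a confidence interval for the Acidil-minus-placebo risk difference.
- Word the conclusion as *no safety signal observed; rates above X% excluded*, with X taken from the stated interval. With no major event in 12 Acidil subjects, X would be 22 (one-sided 95%) or 26 (two-sided 95%).
- Use the same criterion in B1, Hypothesis 1, and say there whether attribution to Acidil matters.

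This changes protocol wording only and needs no extra subjects, visits or data. The cost is a more modest safety statement at the end of the pilot.
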